## 2. Methods and materials

### 2.1. Overview of the study design

This assessor-blinded, bi-center, controlled pilot trial aims to evaluate the feasibility and benefits of a six-week eccentric training program with three weekly sessions (two center-based, one home-based), in individuals with low back pain (musculoskeletal condition) and people with MS (neurological condition). The focus is on the implementation of an eccentric training program directed to the trunk and major lower limb muscle groups. The overall approach includes a four-group bi-center design, in which three groups (A-C) perform an eccentric training program and one group receives standard care (D): (A) control group with healthy, asymptomatic people [CTRL]; B) people with low back pain [LBP]; C) people with MS [PwMS], D); people with MS who are receiving standard care physiotherapy [PwMS_STD_]. A test battery is applied to assess strength, function and patient reported outcome measures prior and following the intervention period. A schedule of enrolment, interventions and assessments is shown in **Fig 1** and the study design and flow in **Fig 2**. The study has been approved by the Ethics Committee of the University of Potsdam, Germany (ref. No. 44/2019) and the Institutional Review Board of the Sheba Medical Center, Tel-Hashomer, Israel (Nr. SMC-6288-19). Any kind of study amendment will be approved by the above-mentioned review boards prior to implementation and will be reported to the trial registry. The study is conducted and performed in agreement with the Declaration of Helsinki. This trial was registered under www.drks.de and the trial number is DRKS00020483 (DRKS, German Clinical Trials Register; 24^th^ January 2020). This paper is further prepared in accordance with the “Standard Protocol Items: Recommendations for Interventional Trials (SPIRIT)” guidelines (see **S1 Table**).

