### 2.2. Participants

The study is performed at two study centers, one in Germany and one in Israel. Participants of the CTRL and LBP group are recruited via the University Outpatient Clinic of the University of Potsdam, Germany. Participants with MS are recruited within the Multiple Sclerosis Center, Sheba Medical Center, Tel Hashomer, Israel. For the rational of a feasibility study a sample size of 12 participants per group is intended [43]. Participants (all sexes) aged between 18 and 65 years are included into this study. Participants eligible for CTRL group are healthy asymptomatic adults, with absence of any acute or chronic LBP. Asymptomatic participants with acute infections, pregnancy, or structural changes of the spine with or without neurological signs contra-indicating physical activities are excluded. Participants eligible for the LBP group need to report a minimum of 3 low back pain episodes within the last 12 month (not exclusively within the last 3 month) and report an average pain score of 3 or above on the numeric rating scale (NRS) within the last 3 months (NRS: numeric rating scale; 0: no pain; 10: worst imaginable pain). People with acute low back pain which occurred for the first time within the last 7 days, acute infections, pregnancy, or structural changes of the spine, with or without neurological signs contra-indicating physical activities are excluded. Participants eligible for PwMS and PwMS_STD_ group need a neurologist-confirmed diagnosis of definite MS according to the revised McDonald criteria, a score of <4.5 on the Expanded Disability Status Scale (EDSS), the ability to walk an equivalent of at least 500m without a walking aid and to be relapse-free for at least 90 days prior to testing. People with MS with cardiovascular disorders, respiratory diseases, the use of steroids or fampridine or other conditions contra-indicating physical activities are excluded.

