Force capacity of the knee flexors and extensors are assessed via isokinetic dynamometry (University Outpatient Clinic—Potsdam: Con-Trex, MJ, Physiomed AG Germany; Sheba Medical Center–Tel Aviv: CSMi Computer Sports Medicine Inc., Stoughton, MA, USA) [54–56]. The isokinetic strength test of maximum voluntary contractions (MVC) is performed within a predefined range of motion of 70° (15° to 85° knee flexion) and at a motion velocity of 60°/s. Flexion and extension are performed in an alternating manner. The isokinetic protocol consists of a warm-up (10 repetitions; 50% of MVC, concentric) followed by five repetitions of concentric MVCs and a familiarization trial of five eccentric flexion/extension movements (50% MVC) followed by five repetitions of eccentric MVCs. Trials are separated by a one-minute break. For the evaluation of maximum force capacity, peak torque (Nm) and work (J) of concentric and eccentric knee flexion and extension will be considered.

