### 2.6 Dta management and statistics

Identifying data of the participants will be recorded once after their inclusion into the study and kept separately from all other study documents. The collected data will be pseudonymized. Documentation and storage of the measurement data takes place on password-protected, department/clinic-internal computers as well as on a web-based documentation form in accordance with the applicable data protection regulations of both countries. All study documents are locked at all times in office spaces only accessible to study team members.

Data of feasibility and surrogate outcomes are analyzed descriptively considering measures of frequency, central tendency, and distribution. The eccentric intervention program will be considered feasible when 70% of the participants adhered to two-third of the training sessions and performed the second measurement after the intervention period [59–62]. To allow conclusions about the potential efficacy of the intervention program only participants that adhered to prescriptions of the exercise program are included in the comparison of baseline and follow-up assessments. Prior to any data analysis plausibility and range checks will be carried out. A per protocol approach is used in the pilot investigation even though an intention-to-treat approach will be preferred for future investigations on the effectiveness of eccentric exercise programs. Possible intervention effects on: patient reported outcomes, mobility, postural control, strength, and muscle-metabolism as well as inflammatory markers are tested by a two-way repeated measures ANOVA (within factor: time, between factor: group allocation). If the variance analysis indicates interaction effects, post hoc testing with respective Bonferroni correction is applied to identify group differences depending on measurement time points. Effect sizes associated with univariate F-statistics will be expressed as eta-squared (η^2^) and effect sizes based on a difference in mean scores will be expressed as Cohen’s d. Study results are planned to be communicated via peer-reviewed international journal publications.

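### For the outcomes measured in all groups, the time-by-group ANOVA in section 2.6 does not isolate the effect of eccentric training; only PwMS versus PwMS_STD does, and LBP has no untrained comparator

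*Protocol article*

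**What the plan says.** Section 2.1 of the protocol article describes a "four-group bi-center design, in which three groups (A-C) perform an eccentric training program and one group receives standard care (D"). The first group is the "A) control group with healthy, asymptomatic people [CTRL"], which therefore also trains. Section 2.2 ties each population to one site: "Participants of the CTRL and LBP group are recruited via the University Outpatient Clinic of the University of Potsdam, Germany", and "Participants with MS are recruited within the Multiple Sclerosis Center, Sheba Medical Center, Tel Hashomer, Israel". Section 2.4.1 states that assignment is random only where that applies. In section 2.4.2 the knee dynamometer differs by centre: "Con-Trex, MJ, Physiomed AG Germany" in Potsdam and a CSMi device in Israel.

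For effects on patient-reported outcomes, mobility, postural control, strength and blood markers, section 2.6 specifies that they are "tested by a two-way repeated measures ANOVA (within factor: time, between factor: group allocation"). It continues: "If the variance analysis indicates interaction effects, post hoc testing with respective Bonferroni correction is applied to identify group differences" by measurement time. No contrast is named, there is no centre term, and neither the number of group levels nor the number of Bonferroni comparisons is given. The comparison of baseline with follow-up is per protocol.

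**The concern.** A group-by-time interaction asks whether the groups change by different amounts. It answers a question about treatment only if the groups differ by treatment and by nothing else that affects change. In this design CTRL, LBP and PwMS receive the same program, and only PwMS_STD receives something else. Any comparison of a Potsdam group with an Israeli group also compares diseases and centres. LBP versus CTRL compares two trained groups: if both benefit equally the contrast is zero, however large the benefit.

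Two errors can follow. A difference in response between populations or centres may be reported as an intervention effect. And the one comparison that does address the intervention may be missed, because it is reached only after a significant omnibus interaction and a multiplicity correction. Section 2.5.2 says the observed changes are to be the basis for later efficacy studies, and section 2.6 chooses the analysis set with potential efficacy in mind, so such a reading would carry forward.

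**Working it through.** **Which outcomes are affected.** Sections 2.4.2 and 2.4.3 separate the common outcomes from the population-specific ones.

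- All four groups: EQ-5D, TuG, 5-STS, sway, knee strength, blood markers. Here the group factor can have four levels.
- MS groups only: SF-36, MSWS-12, MFIS, FES-I. Here the ANOVA is already PwMS versus PwMS_STD by time, which is the right contrast.
- LBP and CTRL only: Chronic Pain Grade and trunk strength. Here the contrast is between two trained groups and isolates no intervention effect.

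**What each pair differs by.**

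| Pair | Treatment | Disease | Centre |
|---|---|---|---|
| PwMS vs PwMS_STD | yes | no | no |
| LBP vs CTRL | no | yes | no |
| PwMS vs LBP or CTRL | no | yes | yes |
| PwMS_STD vs LBP or CTRL | yes | yes | yes |

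**Inputs.** From the documents: four groups and 12 per group ("For the rational of a feasibility study a sample size of 12 participants per group is intended"), so 48 in total. Assumed here: two-sided alpha 0.05, four levels, effects in units of the SD of change, independent groups with equal SD, everyone analysed. The 12 per group is given without power inputs, so there is no power figure to reproduce.

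**Interaction test.** With two time points (M1 and M2) the group-by-time F test equals a one-way ANOVA on change, with 3 and 44 degrees of freedom (4 − 1 and 48 − 4). The noncentrality is λ = n Σ(μᵢ − μ̄)². If one group shifts by s and the other three do not, Σ(μᵢ − μ̄)² = 0.75s², so λ = 12 × 0.75s² = 9s².

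Shift in LBP alone, PwMS equal to PwMS_STD:

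| Shift s (SD) | λ | P(interaction significant) |
|---|---|---|
| 0.3 | 0.81 | 10% |
| 0.5 | 2.25 | 20% |
| 0.8 | 5.76 | 46% |
| 1.0 | 9.00 | 67% |

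If both Potsdam groups shift together, Σ(μᵢ − μ̄)² = s² and λ = 12s². For 0.5, 0.8 and 1.0 SD this gives 25%, 59% and 80%, again with no treatment difference in MS.

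**A real effect looks the same.** If all three trained groups gain 0.8 SD and PwMS_STD gains nothing, λ = 9 × 0.8² = 5.76 and the probability is 46%, the same as when one Potsdam group alone shifts by 0.8 SD. The omnibus result cannot tell these situations apart.

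**Cost of the gate.** For a true PwMS versus PwMS_STD difference of 1 SD, a direct two-sample t test with 12 per arm has noncentrality 1 × √(12/2) = 2.45 on 22 degrees of freedom and power 65%. By simulation, requiring first a significant four-group interaction and then significance at 0.05/k:

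| Comparisons k | Detected |
|---|---|
| 1 | 57% |
| 2 | 51% |
| 3 | 47% |
| 6 | 38–39% |

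At 0.8 SD the figures are about 22% (k = 6) against 47% directly.

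**Dynamometer.** A constant offset cancels in change: 100 to 110 Nm on one device and 120 to 130 Nm on another are both gains of 10 Nm. A scale difference does not cancel: a device reading 15% higher turns 10 Nm into 11.5 Nm.

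**The case against.** The strongest reply is that section 2.6 never says four groups or six pairs. It says group allocation and a respective correction, and several of the listed outcomes can only be two-group. That stands: four levels is an inference, though the natural one for the common outcomes in a trial described as having four groups, and the number of pairs is unknown, which is why a range is shown. For the MS questionnaires the plan already gives the wanted contrast.

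It is tempting to say that regression to the mean in LBP, who are selected on pain, would drive the interaction. The documents do not support this for the four-group outcomes. The back-pain questionnaire is not given to the MS groups, and selection on pain bears directly only on the EQ-5D pain item. Nothing in the documents fixes the size of any shift, and at 0.3 to 0.5 SD the probability is 10% to 20%. It is equally tempting to treat the two dynamometers as a full confounder. They concern knee strength only and, in change scores, only a scale difference matters.

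Two further replies have weight. Comparing populations on an identical program is a stated interest (section 1), so such comparisons need not be forbidden; they need the right label. And the 12 per group was not chosen for power, so the loss through the gate is an illustration, not a failed design target. The calculation also covers M1 and M2 only; blood markers have extra samples around the first session.

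None of this changes the main point: section 2.6 presents the analysis as a test of intervention effects without naming the one comparison that is such a test.

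**Conclusion.** The point holds for the common outcomes. A significant time-by-group interaction can arise from differences between diseases or centres alone, in about 10% to 67% of trials for an LBP-only shift of 0.3 to 1.0 SD. A true MS treatment difference of 1 SD is found in about 57% to 38% of trials through the gate, against 65% directly. These figures rest on the assumed alpha, four levels and effect sizes. The structural argument, from who trains and where each group is recruited, does not depend on them.

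A reader might infer that no group-by-time effect in this trial measures the intervention. That goes too far: PwMS versus PwMS_STD shares disease, centre and device, is the only pair that could be randomised, and does estimate eccentric training versus standard care, subject to the per-protocol restriction. A reader might also infer that the trial's main conclusion is at risk. It is not: the primary outcomes are feasibility measures, analysed descriptively, and the 70% feasibility criterion uses no ANOVA result. The consequence is confined to preliminary efficacy signals. This should be fixed, but it is not critical.

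**What to change.** Reword section 2.6 as follows.

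- Pre-specify the PwMS versus PwMS_STD difference in change, with a 95% CI and not conditional on an omnibus interaction, as the only test of an intervention effect.
- Report LBP and CTRL as within-group changes with CIs.
- Label any LBP versus CTRL or cross-centre comparison as a descriptive difference in response between populations.
- State that changes in LBP are uncontrolled and do not support a conclusion on potential efficacy.

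The change needs no new data, visits or participants. Its cost is that the efficacy statement narrows to the MS contrast, which at 12 per arm will be imprecise (47% power at 0.8 SD).

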#### 2.5.2 Secondary outcomes

Besides the primary outcomes on study feasibility, additional surrogate parameters, such as preliminary assessments of possible intervention effects on overall health status, mobility, and postural control as well as muscle strength, are derived. Changes in the surrogates from baseline to follow-up assessment are considered and form the basis for future multi-center investigations on the efficacy of the eccentric training program. Further, the amount and type of missing data in the specific population groups are evaluated to identify possible bias during the measurement and intervention procedure. All outcome parameters are listed in **Table 1**.

**Table 1 pone.0270875.t001:** Feasibility and surrogate outcomes of the pilot intervention study.

Feasibility Outcomes	Surrogate Outcomes
**Study process:** • recruitment rate • retention rate • drop-out rate **Compliance and adherence:** • performed sessions [N] • adaptations to exercise selection and exercise modification [comments] • exercise intensity: RPE [Borg scale; 6–20] **Safety:** • adverse events [N] • pain [NRS, 0–10] • muscle soreness [NRS, 0–10] **Program evaluation:** • exercises, time, material [5-point Likert-scale]	**Questionnaires:** • EQ-5D • CPG (only LBP) • SF-36, MSWS-12, MFIS, FES-I (only PwMS) **Mobility:** • TuG [s]; 5-STS [s] • 2min-walk test [m] (only PwMS) **Postural Control:** • COP sway length [mm] for bi- & uni-pedal stance **Strength:** • peak torque [Nm] knee flex/ext • peak torque [Nm] trunk flex/ext (only LBP) **Blood Samples:** • creatine kinase • myoglobin • C-reactive protein • interleukins (IL-6, IL-8, IL-10, IL-1β, IL-1ra, IL-4) • tumor necrosis factor-alpha

RPE: rating of perceived exertion; NRS: numeric rating scale; EQ-5D: Questionnaire developed by the EuroQol Research Foundation to assess health status; TuG: Timed Up and Go test; 5-STS: Five-times Sit-to-Stand test; CPG: Chronic Pain Grade questionnaire; SF-36: Short Form 36 Health Survey; MSWS-12: 12-item Multiple Sclerosis Walking Scale; MFIS: Modified Fatigue Impact Scale; FES-1: Falls Efficacy Scale–International.

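### For outcomes measured in all four groups, the post hoc step in 2.6, read naturally, compares group levels at each time point rather than change from baseline

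*Protocol article*

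**What the plan says.** Section 2.6 of the protocol article states that possible intervention effects on patient-reported outcomes, mobility, postural control, strength and blood markers "are tested by a two-way repeated measures ANOVA (within factor: time, between factor: group allocation"). The follow-up step is conditional: "If the variance analysis indicates interaction effects", then "post hoc testing with respective Bonferroni correction is applied to identify group differences depending on measurement time points". No post hoc contrast of change and no baseline adjustment is named. The same section expresses effect sizes for mean differences as Cohen's d, without saying which means are subtracted.

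Section 2.5.2 names the target: "Changes in the surrogates from baseline to follow-up assessment are considered and form the basis for future multi-center investigations".

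Section 2.2 defines the groups by health status. "Participants eligible for CTRL group are healthy asymptomatic adults, with absence of any acute or chronic LBP"; the LBP group needs repeated episodes and a minimum average pain score; both MS groups need a confirmed diagnosis and meet the same criteria. On size, "a sample size of 12 participants per group is intended", on feasibility grounds.

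**The concern.** The omnibus interaction asks whether the groups changed by the same amount, which is the question in 2.5.2. A comparison of levels at M2 asks whether the groups have the same mean at that time. The two questions come apart here in two ways.

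- **Across diagnoses.** Healthy people, people with back pain and people with MS are likely to differ on Timed Up and Go, sit-to-stand, sway, strength and EQ-5D before anyone trains. A difference at M2 may be only that gap carried forward. For knee strength, section 2.4.2 also gives the two centers different dynamometers, and CTRL and LBP are measured in one center and both MS groups in the other. A constant device offset cancels in a contrast of change but stays in a comparison of levels.
- **Within MS.** PwMS and PwMS_STD are the only pair drawn from one population. A test of M2 levels ignores each participant's own baseline and so carries the full between-person variance.

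At stake is how secondary results that are meant to inform later multi-center trials will be read, including any Cohen's d taken forward to a sample size.

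**Working it through.** The protocol has no power calculation, so there is no figure of its own to reproduce.

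**Inputs from the protocol.** Four groups of 12 (2.2); time-by-group ANOVA as gate, then Bonferroni post hoc tests (2.6). Four groups give 4 × 3 / 2 = 6 pairs, or 6 × 2 = 12 comparisons if every pair is tested at both M1 and M2.

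**Assumed, because the protocol gives none of them.** Two-sided alpha 0.05; bivariate normal M1 and M2 with SD 1; within-person correlation r from 0.3 to 0.9; CTRL, LBP and PwMS all improve by 0.8 SD and PwMS_STD by 0; CTRL starts 1.0 or 1.5 SD above PwMS; the two MS groups start level.

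**Formulas.** With two time points the interaction test equals a one-way ANOVA on change. The SD of a change score is √(2(1 − r)). A 0.8 SD effect is therefore 0.8 standard units at M2 and 0.8/√(2(1 − r)) on change:

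- r = 0.3: 0.8/√1.4 = 0.68
- r = 0.5: 0.8/√1.0 = 0.80
- r = 0.7: 0.8/√0.6 = 1.03
- r = 0.8: 0.8/√0.4 = 1.26
- r = 0.9: 0.8/√0.2 = 1.79

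**Simulation, 20,000 trials per scenario.** A rejection counts only if the interaction is significant at 0.05.

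*PwMS vs PwMS_STD, true effect 0.8 SD, alpha 0.05/6:*

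| r | Gate opens | M2 level | Change | ANCOVA |
|---|---|---|---|---|
| 0.3 | 34% | 12% | 12% | 15% |
| 0.5 | 47% | 14% | 20% | 22% |
| 0.7 | 70% | 17% | 37% | 40% |
| 0.8 | 87% | 19% | 59% | 61% |
| 0.9 | over 99% | 20% | 92% | 92% |

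At r = 0.8 the interaction is found in 87% of trials, but the M2 test locates the MS difference in 19%.

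*CTRL vs PwMS, equal change:*

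- At 0.05/6 the M2 test rejects in about 13% (gap 1.0 SD, r = 0.3) to 77% (gap 1.5 SD, r = 0.9). At r = 0.8 it is 31% for a 1.0 SD gap and 68% for a 1.5 SD gap.
- At 0.05/12 with a 1.5 SD gap it rejects in 23%, 32%, 48%, 60% and 68% at r = 0.3, 0.5, 0.7, 0.8 and 0.9.
- Significant at M2 but not at M1: about 6% to 9% over these gaps and correlations (7.6% at r = 0.8, gap 1.5 SD, 0.05/6).
- A contrast of change rejects in about 1% throughout.

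*No group changes (r = 0.8, gap 1.5 SD):* the gate opens in about 5% of trials, and the CTRL vs PwMS test at M2 rejects in about 4% overall.

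**The case against.** The case on the other side is substantial.

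- **The wording is loose.** A group difference that depends on the time point is also an ordinary description of an interaction, so contrasts of change may be intended. This stands as a caution: the level comparison is the natural reading, not the only one. The same edit settles it either way.
- **M1 is tested too.** A reader might infer that up to 77% of such trials would falsely claim a training effect. The documents do not support that. A pair that differs at both M1 and M2 plainly shows a pre-existing gap, and nothing in the protocol says that an M2 difference between diagnoses will be reported as an intervention effect. The misleading pattern, different at M2 only, occurs in about 6% to 9%. That is still well above 1%.
- **The power loss depends on r.** At r = 0.3 the gated tests of level and change are equal, and without the gate the level test does better (20% against 13%). At r = 0.7 the contrast of change still misses 63% of 0.8 SD effects. Much of the low power comes from 12 per group with Bonferroni correction. This stands.
- **MS-only outcomes are already handled.** For SF-36, MSWS-12, MFIS, FES-I and the two-minute walk there are two groups and two time points, so the interaction is itself the test of change, at 0.05 without Bonferroni. Under the same assumptions its power at r = 0.8 is about 84%. This stands and limits the point to outcomes measured in all four groups.
- **These are secondary outcomes of a feasibility pilot**, also analysed descriptively. This stands and limits the severity.

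**Conclusion.** The point holds for outcomes measured in all four groups. On its natural reading, the post hoc rule answers a different question from the one in 2.5.2, in a design whose groups differ at baseline by definition.

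The equal-change error across diagnoses appears at every correlation examined once some group responds differently. The interaction gate contains it only when no group changes. For the two MS groups the loss of power runs from none at r = 0.3 to 92% − 20% = 72 percentage points at r = 0.9. All sizes rest on assumed effects, gaps and correlations.

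A reader might go further and conclude that the planned analysis as a whole cannot test training effects. It can: the omnibus interaction tests change, and the feasibility criterion in 2.6 does not depend on the post hoc step. The change is advisable rather than essential.

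**What to change.** Replace the post hoc sentence in 2.6 with:

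> If the interaction is significant, post hoc tests compare groups on change between the relevant time points (M1 to M2; for blood markers also before to three days after the first session), Bonferroni-corrected over the pairs. For PwMS versus PwMS_STD, the follow-up value is compared with adjustment for the baseline value. Group differences at a single time point are reported descriptively and not interpreted as intervention effects.

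Base Cohen's d on the difference in change, with a 95% confidence interval.

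The blood-marker clause is needed because section 2.4.1 adds samples around the first session to capture the acute reaction, which an M1-to-M2 contrast alone would leave out. Baseline adjustment is proposed for the MS pair because, in the gated simulations, ANCOVA was at least as powerful as the M2 test in every scenario examined.

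The cost is a short text change. It needs no new data, and for M1 to M2 it means 6 contrasts per outcome instead of up to 12. The small downside is that level differences at M2 are no longer formally tested.
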